**1.8 Trial Phase: Phase IIa**

**1.9 STH Programme affiliation:** Endocrinology and Reproduction

**2. Research Question.**

Does antagonism of the glucocorticoid receptor by use of mifepristone (RU486) improve blood pressure and indexes glycaemic control in patients with adrenal adenomas and sub-clinical Cushing’s syndrome?

This is a pilot study to assess if such antagonism has any effect in these patients. A larger study will then be planned based on the outcomes here.

**3. Aim of the Study**

To assess if short term (8 weeks) of antagonism of the glucocorticoid receptor with mifepristone improves metabolic parameters in this patient group as stated above. This is entirely original research. This will form the basis for a larger study. Ultimately it may lead to a diagnostic test that allows stratification of patients to adrenalectomy. This is a completely unmet need in clinical medicine, in an increasingly common clinical problem.

**4.Background**

**The need for study, scientific and clinical justification**

Cortisol excess is associated with increased mortality from cardiovascular disease. Cortisol excess in the general population is now recognised as being common, and is found frequently in patients with adrenal masses incidentally disclosed on CT scans, so called ‘adrenal incidentalomas’ 1. Compared to age, sex and BMI-matched controls, patients with these cortisol-secreting adrenal adenomas are at significantly increased cardiovascular risk with increases in hypertension, impaired glucose tolerance and diabetes, hyperlipoproteinaemia, and increased carotid intima-media thickness 2-5. Although the biochemical cortisol-excess is sufficient to causes these changes, it is insufficient to cause the clinical features typically associated with Cushing’s syndrome 6,7. It is for these reasons that the term ‘Sub-Clinical Cushing’s syndrome’ (SCS) is often applied to this condition.

Post mortem studies show a prevalence of adrenal adenomas of approximately 10% 8. Approximately 5% of all abdominal CT scans disclose an adrenal incidentaloma 1,9. The prevalence increases in an age-related fashion and they are found in 0.2% of abdominal CT scans in patients 20-29 years of age, this rising to approximately 10% in those over 70 years of age 8,9. Between 5-20% of these adrenal masses are associated with SCS 10. Thus, SCS is common in the general population (1% or more of those >70y in hospitalized or health-screened populations), and contributes to overall cardiovascular morbidity and mortality. An ever expanding number of patients with adrenal masses are being found, due to the increasing use of CT in all areas of medicine: in the past decade the number of CT scans performed in the UK has doubled from 1.2 to 2.4 million per year (source Dept of Health, UK - form KH12). This huge increase means that the number of patients identified with SCS is set to rise still further.

The major problem is that management of SCS is *not* established. Approximately 90% of patients with SCS have hypertension, over 60% have impaired glucose tolerance or diabetes mellitus, and osteoporosis 2,3,5,11-15. In SCS there is the potential to permanently reduce these risks, and to improve bone health, by adrenalectomy. In terms of the potential benefit from treating these risk factors, meta-analysis of several large prospective studies has shown that a 5 to 6mm Hg decrease in diastolic blood pressure is associated with a 38% reduction in risk for stroke and a 16% reduction in CHD events 16, whilst a 10 mmHg reduction in systolic blood pressure is associated with a 31% reduction in risk of stroke 17. Moreover, impaired glucose tolerance is associated with a two-fold risk of cardiovascular death 18. Only a very limited number of individuals with SCS have been subjected to adrenalectomy, with the few reported forming parts of studies investigating the biochemical, cardiovascular and bone abnormalities of patients with adrenal incidentaloma. In those that have undergone this procedure improvements have been found in blood pressure (10mmHg drop in systolic BP), lipid profiles, fibrinogen levels, and glycaemic control 3-5,19,20. However, the difficulty facing the clinician is in deciding whether adrenal surgery will be of benefit for a given patient with SCS, and the basis for selection for such permanent and invasive intervention is not established. On follow-up the majority of incidentalomas remain unchanged in size and malignant transformation is rare 21. In contrast to SCS the management of other causes of adrenal incidentaloma is not controversial, and the 4.2% that are phaechromocytomas and the 1.6% that are aldosteronomas 22 are usually considered for surgical excision. Surgery is also indicated if there is a significant increase in size demonstrated on CT scans repeated at intervals.

Given the current lack of knowledge in the management of SCS, we believe that short-term antagonism of cortisol by pharmacological glucocorticoid receptor blockade using mifepristone is a logical means to address these questions, and to test whether this improves clinically important risk factors in this common problem.

Specific questions to be addressed:

1. Does glucocorticoid receptor antagonism with mifepristone improve cardiovascular and metabolic derangements in patients with SCS?

2. Are there markers to predict or explain such a response?

Our approach will allow mechanistic study of the effects of such antagonism, without the inherent risks of surgery, and the opportunity to develop a clinical decision-making tool to inform the critical decision as to whether to proceed to adrenalectomy. We seek to perform an initial pilot study to assess the effects of this treatment and inform the design of a larger study.

Patients with adrenal adenomas with sufficient secretion of cortisol to cause clinical Cushing’s syndrome clearly benefit from adrenalectomy: uncontrolled Cushing’s syndrome has an SMR of 3.8-5.2 23,24, this returning to normal with adequate control of hypercortisolaemia 25. Further insight into effects of the degree of excess glucocorticoids can be gained from important data studying the effects of exogenous glucocorticoids in the Scottish population, where even modest doses were associated with subsequent cardiovascular events, including stroke and myocardial infarction 26. Thus, the degree of hypercortisolaemia is important in determining the cardiovascular and metabolic events, but characterization of this compared to the outcome of any intervention is not established in SCS. To address this question in patients with SCS, one option would be to perform a study randomizing to adrenalectomy in order to assess the efficacy of lowering cortisol. This is, however, a highly interventional means of addressing the issue, and one that may not be to patients’ benefit. Furthermore, such a study could be more easily justified if short-term antagonism of cortisol was shown to be of benefit.

Three main tests are used to demonstrate excess cortisol secretion: urinary free cortisol, dexamethasone suppression tests, and midnight plasma or salivary cortisol 6,7. In SCS urinary free cortisol is usually within the normal range, as this is a relatively insensitive marker of hypercortisolaemia, whilst a post-dexamethasone serum value of >60nM (>1.9ug/dl) in patients with adrenal incidentalomas is associated with excess hypertension 27, as is an elevated midnight cortisol sample 20. Plasma ACTH levels are usually in the lower end of the normal range, reflecting low-grade partial hypothalamo-pituitary-adrenal axis suppression, as a consequence of the low-grade excess autonomous secretion of cortisol from the adrenal. In addition to these tests urinary steroid metabolite analysis by gas chromatography/mass spectrometry (GC/MS) is an invaluable tool allowing detailed analysis of the complete steroid output of an individual and, importantly, by analyzing substrate/product ratios, it facilitates the calculation of measures of steroidogenic enzyme activity. Decreased 5alpha-reductase activity is a specific feature of Cushing’s syndrome and distinguishes it from the polycystic ovary syndrome that is associated with increased 5alpha-reductase activity 28,29, though clinically both conditions may present with features of the metabolic syndrome (obesity, hypertension, impaired glucose tolerance). In addition urinary steroid GC/MS analysis allows the identification of decreased 11beta-HSD2 activity in severe overt Cushing’s syndrome due to the ectopic ACTH syndrome 30, a feature that is not apparent in SCS. GC/MS analysis will allow for a more detailed picture on the nature of glucocorticoid excess in adrenal incidentaloma than urinary free cortisol excretion alone. It will be established whether steroid excretion and metabolism in SCS differs from sex and age-matched patients with similar clinical features (obesity, and arterial hypertension). These controls will be drawn from ‘BUGS’, the Birmingham Urine Gas chromatography/mass Spectrometry database that contains data from more than 500 patients, including cohorts with polycystic ovarian syndrome, arterial hypertension, obesity and impaired glucose tolerance, in addition it contains data on normal controls of various ages with related oral glucose tolerance data (OGTT) data available in a significant proportion.

Mifepristone (11-[4-(Dimethylamino)phenyl]-17-hydroxy-17-[1-propynyl]-[11ß,17ß]-estra-4,9-dien-3-one), a derivative of the synthetic progestin norethindrone, is a potent competitive glucocorticoid and progesterone receptor antagonist, also known as RU 486 31. Mifepristone has approximately three-fold higher affinity for the glucocorticoid receptor than dexamethasone, and 18-fold the affinity of cortisol 32. Mifepristone causes glucocorticoid antagonism by reducing translocation of the receptor to the nucleus and also by antagonising glucocorticoid-dependent transcriptional activity 33. Mifepristone is well absorbed and following oral ingestion has a bioavailability of more than 30%, and peak serum levels are reached within 1-2 hours, with a half-life of 24-48 hours 34. In man administration of mifepristone >200mg/day blocks central and peripheral glucocorticoid action, with resultant activation of the HPA axis: in normal volunteers 200 mg/day of mifepristone for eight days increased plasma, salivary, and urinary cortisol levels secondary to a slight rise in plasma ACTH, but without clinical or biological evidence of cortisol deprivation 35. Thus, these biochemical assessments allow confirmation of blockade of glucocorticoid action. On longer-term treatment, symptoms of adrenal insufficiency are possible, and highlight the need of clinical assessment, as the usual biochemical parameters of cortisol and ACTH levels cannot be reliably interpreted to assess this. Mifepristone-induced adrenal insufficiency can, however, be overcome: administration of dexamethasone 1mg is sufficient to overcome the effects of mifepristone 400mg 32. The efficacy of mifepristone has also been assessed in few patients with severe Cushing’s syndrome. Following the original description in 1985 36 a total of 18 patients in the world literature in whom this drug has been used for this purpose have been described to 2007 37. It has been found to be effective in patients with excess cortisol from adrenal tumours or the ectopic ACTH syndrome, and in reducing clinical parameters including hypertension, glucose homeostasis and psychosis. A study in severe ectopic ACTH syndrome is currently recruiting, with a starting dose of 600mg/day, titrating up to 20mg/kg/day. In addition to the anti-glucocorticoid effects, the anti-progestogenic effects appear at lower doses. The anti-progestogenic effects have also been exploited in the long-term treatment of patients with meningiomas, breast cancer (200-400mg/day) and myomas, with a good safety record (up to 14 years of treatment for meningiomas, mifepristone 200mg/day) 38,39. The anti-progestogenic effects of mifepristone have been also been shown to cause reversible endometrial hyperplasia after six months of therapy 40. Mifepristone is currently licensed at single doses of 600mg to induce medical termination of pregnancy, without evidence of adrenal insufficiency.

A variety of other compounds can be used to lower circulating cortisol by enzymic inhibition of the steroidogenesis in the adrenal, including metyrapone and ketoconazole, which are used routinely in the management of patients with Cushing’s syndrome. These compounds, however, also alter the synthesis of many other steroids, increasing androgenic and mineralocorticoid precursors, and are frequently associated with side effects.

*Hypothesis.*Based on the current literature and established effects of glucocorticoids on cardiovascular and metabolic risk, we hypothesise that mifepristone will improve blood pressure and glucose tolerance in patients with SCS, and that it may be used safely for this purpose.

*Why is the Study needed now?*

Because of the greatly increased use of CT an MR imaging in the UK and abroad, patients with identified SCS are common. Clinicians faced with this problem have no means of deciding how these patients should be best managed. It is for this reason that the recent NIH State of the Science Statement on the ‘Management of the Clinically Inapparent Adrenal Mass “Incidentaloma”, 2002’ 41, highlights the need for a prospective study to characterize sub-clinical hypercortisolism, including associated morbidities, and to establish the benefits of treatment. Although mifepristone has been in clinical use for many years it has never been used for this indication.

This pilot study will assess whether antagonism of low-grade hypercortisolaemia in patients with SCS improves the important established clinical endpoints of hypertension and glucose homeostasis. Furthermore, the design of the study includes assessment of parameters that will allow an understanding of the nature and degree of the mechanism of effect, and the length of time needed to see such an effect. There is clear potential patient benefit in establishing whether such an intervention improves these end points and other clinical parameters, and also in identifying markers that can be used to predict such an effect in clinical practice. The likely timelines for patient benefit would be rapid since the drug intervention is already available, facilitating translation into routine clinical practice.

This approach has not been considered before and is completely novel. All sources of evidence are summarized and referred to in the section above.

The study fits fully with the Endocrinology strategy for STH.

The study will be conducted in compliance with the protocol, GCP and applicable regulatory requirements.

**5. Plan of investigation**

**5.1 Methodology**

The full methodology and justification is given sections 5.2-5.10 below.

**5.2 Design**

This is an open labelled, pilot study over eight weeks at one centre: We feel that given the lack of widespread experience of using the anti-glucocorticoid actions of the drug in man in general, and the lack of data entirely for this indication, that the detailed nature of investigation is justified. As a compromise, the first 5 intervention visits are weekly, and the next two 2-weekly. A screening visit (week -4; visit 1) will also take place up to 4 weeks prior to the first intervention visit (week 0; Visit 2). A follow up visit will take place 72 hours after the last dose. We will recruit 6 individuals with SCS. The overall study design and assessments is shown below, including assessments made for secondary endpoints: Intervention - Mifepristone 200mg BD from week 0-8.

| **Week** | **-4** | **0** | **1** | **2** | **3** | **4** | **6** | **8** | **8** |
| --- | --- | --- | --- | --- | --- | --- | --- | --- | --- |
| Visit | 1 | 2 | 3 | 4 | 5 | 6 | 7 | 8 | 9 |
| Informed Consent |  |  |  |  |  |  |  |  |  |
| Treatment (sc: screening; s: Treatment start; e: Treatment end; fu: Follow up 72 hours after last dose) | Nsc | Ys | Y | Y | Y | Y | Y | Ye | Nfu |
| Resting BP and clinical assessment |  |  |  |  |  |  |  |  |  |
| 24-hour BP (during week of study) |  |  |  |  |  |  |  |  |  |
| OGTT – 0,15,30,60,90,120 mins samples for insulin and glucose |  |  |  |  |  |  |  |  |  |
| U+E |  |  |  |  |  |  |  |  |  |
| LFT |  |  |  |  |  |  |  |  |  |
| TSH |  |  |  |  |  |  |  |  |  |
| FBC |  |  |  |  |  |  |  |  |  |
| Fasting lipids |  |  |  |  |  |  |  |  |  |
| 0900h/2400h salivary cortisol |  |  |  |  |  |  |  |  |  |
| 0900h serum cortisol |  |  |  |  |  |  |  |  |  |
| Plasma ACTH |  |  |  |  |  |  |  |  |  |
| Bone turnover markers – formation, serum osteocalcin; resorption, urine NTX |  |  |  |  |  |  |  |  |  |
| Urinary steroid profile (during week of study) |  |  |  |  |  |  |  |  |  |
| Health-related quality of life questionnaires |  |  |  |  |  |  |  |  |  |

***Inclusion criteria*** Patients will be eligible for inclusion if: they are males and over 18, or postmenopausal women; have an adrenal incidentaloma with benign characteristics diagnosed on CT or MRI; lack clinical features classically associated with Cushing’s syndrome; have evidence of excess cortisol as shown by lack of suppression of serum cortisol on 1mg over-night dexamethasone suppression or 2mg /day 48 hour low-dose dexamethasone suppression testing 41; stable antihypertensive and diabetic medication for two months prior to study entry.

***Exclusion criteria*** will include: evidence of local or systemic malignancy; overt Cushing’s syndrome; severe uncontrolled diabetes mellitus or hypertension; pregnancy; clinically significantly impaired cardiovascular function (e.g. stage IV cardiac failure); severe liver disease (liver enzymes ≥ 3 x the institutional upper limit of normal range); significantly impaired renal function (eGFR <30/min); uncontrolled severe active infection; treatment with approved or experimental steroidogenesis inhibitors, adrenolytic agents, within four weeks of admission; In women, known endometrial cancer, history of endometrial hyperplasia or vaginal bleeding of unknown cause; requirement for inhaled or systemic glucocorticoids for existing disease; impaired mental capacity or markedly abnormal psychiatric evaluation that precludes informed consent.

***Justification of period of study****:* The choice of eight weeks reflects the desire to allow sufficient period for the cardiovascular and metabolic effects of glucocorticoid antagonism to become manifest, and is extrapolated from the effects seen in the few patients with Cushing’s syndrome treated with mifepristone 37.

***Justification of dose and dose interval****:* The dose of 200mg twice daily has been chosen to provide partial blockade of glucocorticoid receptor activity. The interval is twice daily based on the known half-life of the drug and the wish to *partially* block glucocorticoid activity over the 24-hour period, without overt glucocorticoid deficiency, and to minimize the possibility of a rebound effect of increased cortisol exposure at the end of the dose interval, as may happen by using a single dose of mifepristone 400mg/24 hours.

***Drug administration and compliance****:* A check on the blister packs of the tablets issued and therapeutic drug monitoring will be performed at each visit to assess and encourage compliance. All existing medication will be left unaltered for the duration of the study. The first dose of the drug (Treatment start) will be given at Visit 2 (week 0) after baseline tests have been performed. The last dose (Treatment end) will be taken in the morning at Visit 8 (week 8). The drug will be administered 1 hour before food to maximise bioavailability as mifepristone is absorbed rapidly.

***Safety****:* Clinical assessment by BP, P, temperature, weight and questioning for fatigue, headache, anorexia, nausea, arthralgia, myalgia, and abdominal pain (potential glucocorticoid deficiency, a predictable effect of mifepristone based on its known action) will be made at each study visit. Clinical experience is, however, that even total adrenal insufficiency is well tolerated in the absence of physical or infective stressors. For safety purposes each patient will also be issued with written instructions which will tell them what to do if this side effect occurs and with a supply of two dexamethasone 1mg tablets (sufficient to overcome the effects of mifepristone 400mg by taking dexamethasone 1mg/day for 2 days) to be taken on the advice of the investigators if significant symptoms are reported. In such circumstances any study subject will be asked to attend the CRF either that day or the next working day, and data entered into the CRF accordingly, and the subject asked to stop the mifepristone and withdrawn. Other uncommon but documented side effects of mifepristone used at this dose and for this time period include: skin rash (maculopapular), increased eosinophil count, joint pain, hypokalaemia. When used for >3-6 months duration endometrial hyperplasia, uterine fibroma, and endometriosis are described.

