**5.4 Outcome measures**

***Primary end points*** will be the difference at 8 weeks, compared to baseline, in systolic blood pressure (BP) (resting and ambulatory) and 2-hour glucose tolerance during a 75g oral glucose tolerance test. BP will be measured in the sitting position, left arm taken twice, separated by 5 mins, after 10 mins resting (according to British Hypertension Society, UK [BHS] guidelines). 24-hour ambulatory blood pressure will be measured using standard BHS-approved monitors.

The primary endpoints have been chosen, as they are associated with important clinical outcomes. Baseline 24 hour ambulatory BP monitoring will be performed in the week starting treatment between the first visit (screening) and second visit (treatment start) and again at weeks 4 and 8. The daytime and nocturnal BP as determined by 24-hour ambulatory monitoring will be assessed independently and together to take account of the influence of the circadian rhythm in serum cortisol. The baseline glucose tolerance test will be performed on the first day of treatment (treatment start) before the first dose and again at weeks 4 and 8.

***Secondary end points*** will be compared to baseline: 1) the difference in BP and Glucose tolerance at 4 weeks; 2) homeostasis model assessment of insulin resistance (HOMA-IR) 42, and the insulin Sensitivity Index (ISI) 43 at 4 and 8 weeks, as calculated from oral glucose tolerance test: insulin and glucose at -15, 0, 30, 60 and 120 minutes, with oral glucose 75g at time 0 (except for those on insulin therapy, whose investigation will be limited to basal and 120 minute plasma glucose); 3) the difference in the mean plasma 0900h plasma ACTH, and salivary 0900 and 2400h cortisol values at 4 and 8 weeks; 4) the difference in fasting lipids at 8 weeks; 5) the difference in bone turnover markers at 8 weeks; 6) difference in urinary steroid profile at week 8; 7) the difference between depression, quality of life and fatigue questionnaires at 4 and 8 weeks. Tertiary endpoint will be any major cardiovascular adverse events at 8 weeks. Other biochemical safety parameters are summarized in the table above.

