#### *Treatments and Blinding*

This is an open-label non-randomised study. Blinding is therefore not applicable.

*Concomitant therapy*

All medications taken during the four weeks prior to visit two will be recorded. Patients will be discouraged from taking any medication during the study that has not been taken at baseline. An exception is the medication that was required to treat an adverse event. Patients will not take any new prescription or over-the-counter medication during the study unless the Investigator has given their prior consent. Paracetamol is an acceptable concomitant medication, and if necessary, will be prescribed by a Physician. If any medication, is required, the name, strength, frequency of dosing, and reason for its use will be documented in the patient's Case Report Form. As mifepristone is metabolised by the CYP 3A4 enzyme system concomitant use of enzyme inhibitors or enzyme inducers may raise or reduce levels of mifepristone respectively. Mifepristone being an enzyme inhibitor of CYP 3A4 may lead to an increase in serum levels of drugs that are CYP 3A4 substrates. This factor should be taken into consideration if any of these drugs are taken.

*Contraception*

All male patients, including those who have been vasectomised, will be asked to use barrier contraception (e.g condom + spermicide) if they are sexually active with premenopausal women, throughout the whole trial and for a period of seven days after the last dose. This is to ensure there is no inadvertent transfer of mifepristone to a fetus in the semen.

Further, male patients and premenopausal partners should use two highly effective methods of contraception for three months from the last dose of mifepristone. This is to allow the passage of one spermatogenic cycle of 60-70 days after treatment has stopped before stopping contraceptive measures.

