##### *Efficacy evaluation*

The primary efficacy analysis can be run on both the ITT and PP populations in order to take into account the response of patients prematurely withdrawing from the study for any reason.

The primary efficacy evaluation is based on the primary efficacy parameters given. In cases of premature withdrawal from the study, at least one post-baseline measured efficacy parameter will be carried forward. The primary efficacy variable is then derived as the proportion of patients with successful treatment outcome after 8 weeks using the following criteria to define treatment outcome:

i) change in the resting and 24-hour ambulatory blood pressure.

ii) change in 2-hour glucose on OGTT.

*Safety of investigators* – There are no specific issues

*Participants rights to information and consent, confidentiality and privacy*

This will be in accordance to GCP guidelines. In terms of informed consent, patient recruitment will be at time after completion of usual investigation according to clinical practice. Since there is no specific time window needed for intervention, potential participants will have adequate time to consider their involvement and what it entails.

*Storage of data*

Patient data will be in a secure repository for 15 years.

*Ethnic and racial diversity*

This is a pilot study and thus the numbers are small. There is no evidence of altered adrenal function in different ethnic groups. In terms of information and consent if any potential study participant is not fully competent in the English language appropriate interpreters and translation of the information sheet and consent will be undertaken. Given the predominant Caucasian population of our catchment area it is likely that the participants will be Caucasian.

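### The two-month medication stability rule covers the primary endpoints but not the lipid, bone and questionnaire endpoints, so a drug started shortly before screening can bias their change from baseline

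*Protocol*

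**What the plan says.** The inclusion criteria in section 5.2 require "stable antihypertensive and diabetic medication for two months prior to study entry". The other drug-related criteria there are exclusions: "treatment with approved or experimental steroidogenesis inhibitors, adrenolytic agents, within four weeks of admission" and "requirement for inhaled or systemic glucocorticoids for existing disease". None of them concerns lipid-lowering, bone-active or psychotropic drugs.

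Once a patient is in, section 5.2 (Drug administration and compliance) states: "All existing medication will be left unaltered for the duration of the study". Section 8.0 (Concomitant therapy) adds that "All medications taken during the four weeks prior to visit two will be recorded" and that "Patients will be discouraged from taking any medication during the study that has not been taken at baseline". It also makes new drugs during the study subject to the investigator's prior agreement.

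Section 5.4 makes the primary endpoints the week-8 difference from baseline in systolic blood pressure and 2-hour glucose. Its secondary endpoints include "4) the difference in fasting lipids at 8 weeks; 5) the difference in bone turnover markers at 8 weeks", and the depression, quality-of-life and fatigue questionnaires at weeks 4 and 8. Section 5.3 describes an open-label, non-randomised, exploratory study whose secondary endpoints are analysed like the primary ones. Section 5.2 sets the number of patients at six.

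**The concern.** In a single arm, a change from baseline is attributed to the study drug only so far as nothing else is changing. The protocol accepts this for blood pressure and glucose by asking for two months of stable treatment in the two matching classes. It gives no such protection to lipids, bone markers or the questionnaires, although they are analysed in the same way.

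Drugs acting on these endpoints are plausible in this population: section 4 lists hyperlipoproteinaemia and osteoporosis among the features of these patients. The direction of bias also matters. Section 4 cites better lipid profiles after adrenalectomy, so a recently started lipid-lowering drug would imitate the hoped-for result. Section 5.4 predicts a rise in osteocalcin, and a recently started bone-active drug could imitate or hide such a change. The pilot is meant to inform a larger study, and section 11 expects it to identify a marker of effective antagonism. A spurious signal in a secondary endpoint could therefore be carried forward.

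**Working it through.** The protocol gives no figure to reproduce: there is no power calculation and no assumed effect. The check compares the relevant rules and adds one line of arithmetic.

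**Step 1. Which endpoints does the stability rule cover?**

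| Endpoint (section 5.4) | Matching drug class | Stability required before entry? |
| --- | --- | --- |
| Systolic blood pressure (primary) | antihypertensive | yes, two months |
| 2-hour glucose (primary) | diabetic | yes, two months |
| Fasting lipids (secondary) | lipid-lowering | no |
| Bone turnover markers (secondary) | bone-active | no |
| Depression, quality of life, fatigue (secondary) | antidepressant or other psychotropic | no |

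**Step 2. Does other text close the gap?** Take a lipid-lowering drug begun just before Visit 1. Visit 1 falls up to four weeks before Visit 2.
- Eligibility: no criterion applies.
- On study: the drug counts as existing medication and continues unaltered.
- Limits on new drugs: they apply during the study and to drugs not taken at baseline, so they do not reach it.
- Medication record: the drug is listed because it was taken in the four weeks before Visit 2. The text does not say that start dates are recorded, does not make a recent start a ground for exclusion or delay, and states no use of the record in the analysis.

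A drug begun between Visit 1 and Visit 2 is less clear. If the study is taken to run from Visit 1, that start would already need the investigator's agreement. The protocol does not say whether study entry means Visit 1 or Visit 2.

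**Step 3. Size.** Let E be the full effect of the other drug on an endpoint, f the fraction of it that arises after baseline, k the number of such patients and n = 6.

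Shift in mean change = k × f × E / n

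- k = 1: f × E / 6, about 17% of f × E
- k = 2: f × E / 3, about 33% of f × E

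Neither E nor f is in the documents. For scale only, assume E between 30% and 60% of baseline and similar baselines across patients. With k = 1:

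- f = 1: 30/6 = 5% to 60/6 = 10%
- f = 0.5: 15/6 = 2.5% to 30/6 = 5%

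With no concurrent control, nothing subtracts this shift.

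**The case against.** The strongest reply is that the protocol already protects what matters most. The primary endpoints are matched by the two named classes, the analyses are declared descriptive and exploratory, and a placebo-controlled study is to follow. Section 8.0 records recent medication and restricts new drugs. With six patients, a recorded recent start could be seen and that patient shown separately. All of this stands and lowers the severity. It does not close the gap, because recording a drug does not prevent bias and starts before Visit 1 stay outside the restriction.

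Four stronger readings are tempting, and the documents do not support them.
- **That a primary endpoint is exposed as well.** This needs a blood-pressure-lowering drug prescribed for another reason to fall outside the term antihypertensive. The term can equally mean the drug class, so the reading is strained.
- **That such drugs are likely to be started at work-up.** Section 8.0 says only that "patient recruitment will be at time after completion of usual investigation according to clinical practice", and adds that no particular time window is needed. Sections 5.6 and 5.7 describe patients already evaluated. Nothing shows that treatment is begun then.
- **That a full shift is probable.** If 5%, 10% or 20% of recruits had started such a drug within two months, the chance of at least one in six would be 1 − 0.95⁶ = 26%, 1 − 0.90⁶ = 47% or 1 − 0.80⁶ = 74%. These prevalences are assumptions. The calculation also counts starts many weeks before baseline, for which f may be well below 1, so these chances cannot be paired with the full-effect shift.
- **That the two causes can never be separated.** For a start visible in the medication record, they can be partly separated by showing results with and without that patient.

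**Conclusion.** The gap is real and limited. The stability rule protects systolic blood pressure and 2-hour glucose. It leaves fasting lipids, bone turnover markers and the three questionnaires open to the continuing effect of a drug begun shortly before screening. One such patient moves the mean change by one sixth of the part of that effect arising after baseline. How large that part is, and how many patients would be affected, cannot be taken from the documents. The conclusion rests on the wording of the criteria and on there being six patients and no control arm. It is a cheap improvement worth making, of modest weight because the endpoints are secondary and the study is an exploratory pilot.

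**What to change.** In section 5.2, extend the criterion to read: *stable antihypertensive, diabetic, lipid-lowering, bone-active and antidepressant or other psychotropic medication for two months prior to Visit 2*. Naming Visit 2 also settles what study entry means.

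In addition, collect start dates with the medication record in section 8.0, and report the affected secondary endpoints with and without any recent starter found there.

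The cost is one line of eligibility text and a short reporting rule. A few candidates may wait up to two months or be passed over, which is a small loss with 50 eligible patients for six places (section 5.7). No patient's treatment needs to change. A freeze on all long-term medication, or a bar on weight-loss or exercise programmes, would go further than this point justifies.
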